##### Demographics and clinical assessment of cerebellar motor syndrome

Demographics including years of education and employment, educational achievements as well as occupational and marital status will be recorded. For patients, medical records and available brain scans will be evaluated. Age of onset, disease duration and in case of genetically proven nucleotide repeat diseases the repeat length will be documented. Furthermore, a detailed medical history will be taken, and a neurological examination will be performed in every participant. Severity of cerebellar ataxia in patients will be evaluated using different clinical ataxia scales: The Scale for the Assessment and Rating of Ataxia (SARA) [13] will be used because of its widespread use. In addition, the International Cooperative Ataxia Rating Scale (ICARS) [14] will be used because it includes rating of cerebellar oculomotor deficits. Its short form – BARS – [15] will be used to enable direct comparison with the original US-American validation study. The SpinoCerebellar Ataxia Functional Index (SCAFI) [16] will be assessed because it allows for a more objective quantification of motor deficits. Finally, non-ataxia signs will be assessed semi-quantitatively using the Inventory of Non-Ataxia Signs (INAS) [17].

##### Assessment of the CCAS Scale

The CCAS Scale will be administered in each participant at least once. In the validation process of version A, at least 40 patients and 40 controls will receive a follow-up examination with the same version of the scale to determine test-retest and interrater reliability (≥ 20 patients and ≥ 20 controls, respectively). Retesting will be done with the same version because equivalence of versions A-D has not yet been shown (see [10] and Supplements). Follow-up will take place within an interval of 14 to 56 days. A time interval is favored instead of a fixed time span between test and retest (e.g. exactly 14 days) to control for learning effects by correlating retest results with different retest time intervals.

To assess construct validity of the German version of the CCAS Scale a detailed neuropsychological testing will be done in a subset of patients (*n* ≥ 20) and controls (*n* ≥ 20) using well-established neuropsychological test batteries available in German. These will comprise the logical memory test (part I and II) of the Wechsler Memory Scale – 4th edition (WMS-IV) [18], the copy immediate and delayed recall of the Rey–Osterrieth Complex Figure Test (ROCFT) [19], and the letter-number sequencing task of the WAIS-IV [20]. These tests measure the same cognitive domains as corresponding items of the CCAS Scale. Furthermore, the German version 3 of the MoCA [21] will be assessed for direct comparison with the CCAS Scale. Finally, the Patient Health Questionnaire (PHQ-9) [22] and the German version of the EuroQuol – 5 dimension – 3 level (EQ-5D-3L) questionnaire [23] will be administered.

Validation of parallel versions of the CCAS Scale will be done the same way as for validation of parallel German versions of the MoCA [21]. Each parallel version (B/C/D) of the CCAS Scale will be tested against version A. Testing of version B/C/D and version A will be done on the same day, with the order being randomized between participants.

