**Methods:**

A preliminary German version has been created from the original CCAS Scale using a standardized translation procedure. This version has been pre-tested in cerebellar patients and healthy controls including medical experts and laypersons to ensure that instructions are well understandable, and that no information has been lost or added during translation. This preliminary German version will be validated in a minimum of 65 patients with cerebellar disease and 65 matched healthy controls. We test whether selectivity and sensitivity of the German CCAS Scale is comparable to the original CCAS Scale using the same cut-off values for each of the test items, and the same pass/ fail criteria to determine the presence of CCAS. Furthermore, internal consistency, test-retest and interrater reliability will be evaluated. In addition, construct validity will be tested in a subset of patients and controls in whom detailed neuropsychological testing will be available. Secondary aims will be examination of possible correlations between clinical features (e.g. disease duration, clinical ataxia scores) and CCAS scores.

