##### Data analysis

Selectivity and sensitivity will be assessed using the same cut-off values for individual test items, and the same three pass/ fail criteria determined in the original study by Hoche et al. [10] (that is: possible CCAS = one test failed; probable CCAS = two tests failed; definite CCAS = three or more tests failed). To assess selectivity the percentage of true negatives will be calculated, that is the percentage of controls which have been correctly identified as controls [number of controls identified as controls/ true number of controls in the sample * 100]. To assess sensitivity the percentage of true positives will be calculated, that is the percentage of patients which have been correctly identified as patients [number of patients identified as patients/ true number of patients in the sample * 100]. In case selectivity and sensitivity falls below the values of the original CCAS Scale, selectivity and sensitivity of individual tests will be assessed. Cut-off values of single test items and/ or cut-offs defining (possible/ probable/ definite) CCAS will be adjusted to achieve high selectivity and reasonable sensitivity – comparable to the values of the original CCAS Scale.

Differences between patient groups (pure cerebellar disease vs. patients with additional extracerebellar involvement) will also be analyzed. We want to verify that difficulties in verbal registration and delayed verbal recall are indicative of extracerebellar involvement (“red flags”). In further accordance with Hoche et al. [10], Cronbach’s alpha will be used to assess the inter-relatedness of the individual test items, i.e. internal consistency.

To study construct validity of the CCAS Scale subtests of validated German versions of neuropsychological test batteries will be used as the external criterion. We will compare the percentage of patients diagnosed with CCAS based on a detailed neuropsychological test battery with the percentage of patients identified by the CCAS Scale.

Finally, correlations between age, disease duration, severity of cerebellar motor symptoms (measured by clinical ataxia scores), and total CCAS sum score will be calculated. All raw data (thus total number of failed tests respective total sum score and sub scores on single test items) will be tested for normal distribution using Kolmogorov-Smirnov tests. Parametric or non-parametric tests will be applied depending on distribution and final sample size.

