We are interested whether the scale is able to screen for CCAS in patients with degenerative diseases, but also suffering from cerebellar stroke or surgical lesions due to cerebellar tumors. In the validation study of the original American English CCAS Scale only few patients with focal cerebellar lesions were tested [10]. In part of the patients with focal lesions brain MRI scans will be available. This will allow to map dysfunction in the different cognitive domains to lesions in specific cerebellar regions. For example, we expect that language dysfunction is associated with lesions of the right posterolateral cerebellar hemisphere, and visuospatial disabilities with lesions of the left posterolateral cerebellar hemisphere [6].

A limitation of the CCAS Scale is that detection of the neuropsychiatric abnormalities highly depends on the examiner’s expertise. The authors of the US-American original were aware of this weakness and gave this item (“Affect”) a weak denominator for the total sum score [10]. Additionally, administration of more detailed scales of neuropsychiatric dysfunction are recommended [24]. In future studies, expert neuropsychiatric assessments would be of interest as a further external criterion. Furthermore, testing of construct validity has some limitations. We will perform detailed neuropsychological testing only in a subset of patients. More importantly, although the core symptoms of CCAS are well described, as yet there are no standard criteria to diagnose CCAS based on detailed neuropsychological testing. Another approach to test construct validity would be to compare CCAS scores in patients with cerebellar diseases and patients with non-cerebellar neurological diseases in the future. Despite these limitations the CCAS Scale has been shown to be more sensitive to detect cognitive and affective changes in cerebellar disease than the Mini-Mental State Examination and the Montreal Cognitive Assessment [10]. The validated German CCAS Scale will allow trained healthcare personnel to screen for cognitive and affective symptoms in patients with cerebellar diseases in German-speaking countries.

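### Interrater reliability drawn from a follow-up 14 to 56 days later would combine rater, occasion and practice variation, giving a lower bound on rater agreement

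*Protocol article*

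**What the plan says.** The abstract of the protocol article lists interrater reliability as a property in its own right: "internal consistency, test-retest and interrater reliability will be evaluated". The section Assessment of the CCAS Scale fixes where the data come from. For version A, the plan is that "at least 40 patients and 40 controls will receive a follow-up examination with the same version of the scale to determine test-retest and interrater reliability", split as "≥ 20 patients and ≥ 20 controls, respectively". The timing is given once and without exception for either half: "Follow-up will take place within an interval of 14 to 56 days". The same form is used both times: "Retesting will be done with the same version because equivalence of versions A-D has not yet been shown".

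The article recognises practice. The variable interval is chosen "to control for learning effects by correlating retest results with different retest time intervals". The section describes no scoring of one administration by two raters, and it does not say who conducts the follow-up. The Data analysis section describes no step that would separate rater variation from occasion variation.

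On examiner dependence, the Perspective section says that "detection of the neuropsychiatric abnormalities highly depends on the examiner’s expertise". That remark concerns the Affect item.

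**The concern.** Interrater reliability asks how far two examiners differ on the same person in the same state. If the second score comes from another examiner some weeks later, on material the participant has already seen, the difference between the two scores has three sources: the examiner, the participant's day-to-day variation, and practice. Two scores per person cannot separate them. The resulting figure is a different-rater test-retest coefficient. Even examiners who agree perfectly would score no higher than the scale's own retest stability.

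What is at stake is how the figure can be used. The study recruits at several centres, and a web-based training tool is planned after validation. A modest coefficient would not show whether examiner training, fluctuation in the participants or practice was responsible.

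**Working it through.** **The plan's own figure.** Reading *respectively* as two subsets, 20 (test-retest) + 20 (interrater) = 40 per group, which matches the stated minimum of 40 patients and 40 controls. Over both groups this gives 40 + 40 = 80 pairs. The article states no target coefficient or precision for these subsets, so there is no power calculation to reproduce. All ICC and practice values below are assumptions.

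**Model.** Set between-person variance to 1. Let *o* be occasion variance, *r* rater variance and *d* the mean practice gain in between-person SDs. The components are taken as additive and non-overlapping.

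- Rater ICC on one administration = 1/(1 + r)
- Same-rater retest ICC = 1/(1 + o)
- Delayed different-rater ICC = 1/(1 + o + r)
- The same as an absolute-agreement coefficient = 1/(1 + o + r + d²/2)

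**Attenuation.** For a true rater ICC of 0.95, r = 1/0.95 − 1 = 0.0526.

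| Same-rater retest ICC | o | No shift | d = 0.3 (d²/2 = 0.045) | d = 0.5 (d²/2 = 0.125) |
|---|---|---|---|---|
| 0.70 | 0.4286 | 1/1.4812 = 0.675 | 0.655 | 0.623 |
| 0.80 | 0.2500 | 1/1.3026 = 0.768 | 0.742 | 0.700 |
| 0.90 | 0.1111 | 1/1.1637 = 0.859 | 0.827 | 0.776 |

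With perfect raters (r = 0) and no shift, the result is the retest ICC itself: 0.70, 0.80 or 0.90. The two shift columns apply only to an absolute-agreement coefficient. A consistency coefficient ignores a uniform shift.

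**Can the test-retest half serve as a benchmark?** The approximate 95% CI is tanh(atanh(ICC) ± 1.96/√(n − 1.5)). For an ICC of 0.80, atanh = 1.0986.

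- n = 20 (one group): half-width 1.96/√18.5 = 0.456, giving 0.57 to 0.91.
- n = 40 (patients and controls pooled): half-width 1.96/√38.5 = 0.316, giving 0.65 to 0.89.

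For two independent subsets the half-width of the difference on the z scale is 1.96·√(2/(n − 1.5)), which is 0.644 for n = 20 each and 0.447 for n = 40 each. Against a retest ICC of 0.80, the different-rater ICC would have to fall to tanh(1.0986 − 0.644) = 0.43, or tanh(1.0986 − 0.447) = 0.57, before the difference reached two-sided 5%.

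**Does the interval correlation help?** It has 80% power only for |r| = tanh((1.96 + 0.84)/√(n − 3)), which is 0.59 for n = 20 and 0.43 for n = 40. It can show whether practice differs between day 14 and day 56. It does not measure the gain common to all intervals, and it contains no information on raters.

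**What a joint model could deliver.** Take 40 same-rater and 40 different-rater pairs, with o = 0.25 and r = 0.0526. Within-person variance is 0.250 in the same-rater arm and 0.303 in the different-rater arm. With about 39 degrees of freedom each, the standard errors are 0.250·√(2/39) = 0.057 and 0.303·√(2/39) = 0.069. The excess is 0.053 with SE √(0.057² + 0.069²) = 0.089, so the 95% interval runs from about −0.12 to 0.23. The upper limit corresponds to a rater ICC of 1/1.23 = about 0.81. The excess targets the right quantity, but it is imprecise.

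**The case against.** The strongest objection is that the article does not say who conducts the follow-up or which two scores are compared. A reader might infer that it states outright that a second rater examines the interrater half weeks later. It does not. Two raters scoring the follow-up session together would also fit the sentence, and the full protocol or supplement may settle the procedure. This stands as a limit on certainty. The different-rater reading is still the more natural one: participants are divided between the two purposes, and jointly scored participants would not need a follow-up visit to yield interrater data.

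A reader might also infer that the source of disagreement cannot be identified at all. That goes too far. The parallel test-retest half uses the same version and interval, so it gives an indirect benchmark, although the calculation shows how loose that benchmark is. The interval correlation is a genuine, partial attempt to address practice.

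A reader might take the Perspective remark on examiner expertise as a weakness of the whole scale. It concerns the Affect item, which the article says carries little weight in the total score. Nor does the article set a threshold by which a coefficient of, say, 0.80 would count as poor.

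Finally, separate administration has a merit. It captures differences in how examiners deliver items and elicit responses, which shared scoring of one session misses. The choice is therefore a trade-off, and same-session scoring is not simply superior.

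**Conclusion.** The concern holds in a limited form. On the natural reading, the planned interrater figure is a different-rater test-retest coefficient. It errs in the conservative direction: it understates rater agreement and, in expectation, is capped by same-rater retest reliability. For a true rater ICC of 0.95 it would appear as about 0.68 to 0.86 across assumed retest ICCs of 0.70 to 0.90. A practice shift lowers it further only if absolute agreement is used. These sizes rest on assumed ICCs and an additive variance model, since the article supplies no values. Neither the interval correlation nor an informal comparison with the test-retest half resolves the mixture. Selectivity and sensitivity, the main targets of the validation, are untouched. The change is worth making because interrater reliability is a stated aim and the change is cheap.

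**What to change.** State who rates the follow-up. Randomise the follow-up participants within site to the same or a different rater. Fit one variance-component model to all 80 or more pairs, with fixed effects for session and for patient/control group. Estimate rater variance as the excess of different-rater over same-rater within-person variance, and report it with its confidence interval. Label the raw different-rater coefficient as different-rater test-retest reliability, not interrater reliability.

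The cost is an allocation list, some scheduling within sites and one model, with no added participants. The downside is the imprecise rater component shown in the working.

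Where a second rater is already available, independent scoring of one administration may be added as a measure of scoring agreement. The report should note that it does not capture differences in how examiners administer the scale. It would be more precise: for an ICC of 0.95 scored twice in 40 people, the same interval formula gives tanh(1.832 ± 0.316), or about 0.91 to 0.97. It requires two raters for the same administration.

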
## Methods

### Study aims

The first primary aim of this study was to create preliminary German versions of the CCAS Scale. The second primary aim will be their validation in a large cohort of patients with various cerebellar disorders and healthy age-, sex-, and education-matched controls. Secondary aims will be to examine possible relationships between clinical features such as disease duration or severity of cerebellar motor symptoms, and the CCAS score.

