## Perspective

Clinical ataxia scales have been validated to rate the severity of motor symptoms in cerebellar disease [13–17], but so far there has not been a validated clinical scale to screen for the presence of the Cerebellar Cognitive Affective/ Schmahmann Syndrome (CCAS), and quantify CCAS severity. Only recently, Schmahmann and collaborators have developed and validated a promising screening tool for the CCAS – the CCAS Scale – for an American English-speaking population [10]. Till now, no validated German versions of the scale exist. German versions of the CCAS Scale are highly desirable to screen for the presence of CCAS in a clinical setting, but also for patient characterization and stratification in future therapeutical trials. The CCAS sum score may also serve as a therapeutic marker, but this would need future studies to show its sensitivity to change, and if this would be the case, its treatment responsiveness. In this multicenter study, four parallel versions (A-D) of the German CCAS Scale will be validated in a large cohort of German-speaking patients with cerebellar disorders. The parallel versions will allow multiple testing without practice effects.

The primary aim of our validation study is to show high selectivity, that is to show that the German versions of the scale are able to differentiate between patients and controls. We will test whether the pass/ fail criteria used to determine the presence of CCAS in the original scale also apply for the German scale. Cut-off values of individual test items and the pass/ fail criteria shown in Fig. 1 are taken from the US-American original and may change depending on findings in the German validation cohort. Furthermore, future studies are needed to test for possible age effects, and the need for age-dependent cut-off values and pass/ fail criteria. After full validation of the scale the implementation of a web-based training tool is planned.

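### Correlating retest results with the retest interval can show decay of a practice effect but cannot control for learning in the version A retest

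*Protocol article*

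**What the plan says.** All the relevant text is in the protocol article, Methods, Assessment of the CCAS Scale.

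- Same form at retest: "Retesting will be done with the same version because equivalence of versions A-D has not yet been shown".
- Timing: "Follow-up will take place within an interval of 14 to 56 days".
- Reason for a range: "A time interval is favored instead of a fixed time span between test and retest", and the stated purpose is "to control for learning effects by correlating retest results with different retest time intervals".
- Numbers: "at least 40 patients and 40 controls will receive a follow-up examination with the same version of the scale", for test-retest and interrater reliability ("≥ 20 patients and ≥ 20 controls, respectively").

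The Data analysis section does not return to learning in the version A retest. The randomised order on the same day belongs to the comparison of versions B, C and D with A. The only other remark on practice, in Perspective, also concerns those versions: "The parallel versions will allow multiple testing without practice effects".

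**The concern.** The article names one analysis and gives it the task of controlling for learning. Learning on a repeated form shows as a shift from first to second test. A correlation with interval measures something else: whether results differ between people retested sooner and people retested later. If everyone gains and keeps the gain for eight weeks, there is nothing for the correlation to find.

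Practice is plausible here because the same items are repeated, among them verbal registration, delayed recall, similarities and category switching (Background). Test-retest reliability is part of validating version A, and Background says the sum score is meant for follow-up of individual patients. At stake is whether a better second score can be told apart from a practice gain, and whether the agreement figure can be read correctly.

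**Working it through.** The article gives no effect size, SD, reliability or power for the retest, so there is no stated figure to reproduce.

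**Inputs from the article.** Interval 14 to 56 days, a width of 42 days. At least 40 patients and 40 controls retested, with at least 20 of each per reliability purpose. So n = 40 is one purpose with patients and controls pooled, n = 80 is everyone retested, and n = 20 is one group for one purpose.

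**Assumptions.** Score SD 1 at each occasion; intervals spread uniformly; test-retest reliability ρ = 0.8 (range 0.7 to 0.9); practice gain 0.4 SD, either constant or falling linearly to zero by day 56; two-sided 5% tests.

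**Step 1: a gain that persists.** Write the second score as Y2 = T + e2 + g(t) and the first as Y1 = T + e1, where T is the person's level, e1 and e2 are errors and t is the interval, unrelated to T and the errors.

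- Cov(Y2, t) = Cov(g(t), t), and Cov(Y2 − Y1, t) = Cov(g(t), t).
- If g(t) = g for every t, both are zero.

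The expected correlation is therefore zero for the second score and for the change score, for any g and any ρ. Simulation (20,000 runs per setting, constant gain of 0.5 SD, ρ 0.7 to 0.9, n = 20, 40, 80) gave rejection of 4.8% to 5.3% throughout, which is the false-positive rate.

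The mean change does see such a gain. With ρ = 0.8 the SD of change is √(2 × 0.2) = 0.632. At n = 40 its standard error is 0.632/√40 = 0.10, so a 0.4 SD gain is 4 standard errors and the paired t test has power of about 97%. The range is 89% at ρ = 0.7 to nearly 100% at ρ = 0.9.

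**Step 2: a gain that fades completely by day 56.** This is the most favourable case for the planned correlation.

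- SD of g(t) = 0.4/√12 = 0.115.
- Second score with interval: r = −0.115/√(1 + 0.115²) = −0.115.
- Change with interval: r = −0.115/√(0.4 + 0.115²) = −0.180.

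Power by Fisher's z, Φ(|atanh r|·√(n − 3) − 1.96) plus the negligible opposite tail, and for the mean change (mean 0.2, SD 0.643) by the paired t test:

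| n | second score v interval | change v interval | mean change |
|---|---|---|---|
| 20 | 8% | 12% | 26% |
| 40 | 11% | 20% | 48% |
| 80 | 17% | 36% | 79% |

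Simulation agrees to about one percentage point. For ρ from 0.7 to 0.9 at n = 40, change v interval runs from 15% to 34%, while the second-score figure stays at 11%, because differences between people remain in that score.

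**Step 3: smallest correlation detectable with 80% power.** r = tanh((1.96 + 0.84)/√(n − 3)) = 0.59, 0.43 and 0.31 for n = 20, 40 and 80. The expected values in Step 2 are well below these.

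**Step 4: effect on the agreement figure.** With ρ = 0.8 and a constant 0.4 SD gain, a consistency-type coefficient stays at 0.80. An absolute-agreement coefficient adds the occasion variance 0.4²/2 = 0.08, giving 0.8/(0.8 + 0.08 + 0.2) = 0.74. Only the second kind registers the gain.

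**The case against.** The strongest reply is that this is a condensed article. The phrase about retest results sits in a paragraph on reliability and may mean second scores, change scores or agreement. A fuller plan may also hold a mean difference or a suitable coefficient, and leaving those out of an article is no fault.

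Much of this stands. The claim that differences between people swamp the correlation holds only if second scores are meant. Even then, using change raises power only from about 11% to 20% at n = 40, so both are weak. The absence of a mean-change analysis is not counted here. None of this rescues the stated purpose: under any of these readings, a gain shared by all intervals leaves no trace in a correlation with interval.

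A reader might infer more than the article supports:

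- **That retest pass rates will be biased.** No retest pass rate is named as an outcome, and nothing says second administrations enter the selectivity and sensitivity percentages.
- **That the study will give false reassurance about repeated testing.** The reassurance in Perspective rests on the parallel versions, not on this correlation.
- **That a null correlation will be reported as absence of learning.** No rule for interpreting it is given.
- **That late returners differ from early ones.** How dates within the window are set is not described, so this is conjecture.

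A variable interval and reuse of the same version are acceptable in themselves.

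**Conclusion.** The point holds in a limited form. The article assigns control of learning in the version A retest to an analysis that can at most detect fading of a practice gain. For a gain that persists from day 14 to day 56, detection is about 5%, the false-positive rate. That result needs no assumption about gain or reliability, only that the interval is unrelated to ability and error.

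The power figures for a fading gain rest on the assumed 0.4 SD, the assumed reliability and uniform intervals. A larger gain that fades fully would be easier to see. The loss from using second scores instead of change is conditional on that reading of the wording.

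The consequence is confined to interpreting test-retest agreement and repeat use of version A. The main validation result, selectivity and sensitivity of patients against controls, is not affected. The change is worth making because a stated safeguard does not do its job and the repair uses data already planned.

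**What to change.** Replace the stated purpose of the interval analysis with three sentences:

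1. The practice effect in the version A retest is estimated as the mean retest-minus-first change with a 95% confidence interval, separately for patients and controls.
2. Test-retest reliability is reported with an absolute-agreement coefficient, so that a systematic gain lowers it.
3. As a secondary check on decay, change (not the retest score) is regressed on interval with group in the model. A null result is not taken as evidence that learning is absent.

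The 14 to 56 day window can stay as it is, and random allocation of the interval is not required. The cost is slightly more analysis work, with the same participants and visits.
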